### Statistical Methods

This study combines the A’Hern single-arm decision framework with a randomized 2-arm design. The single-arm decision framework is applied to the GET and CBT arms to evaluate the coprimary aims of feasibility and acceptability in the primary study cohort of patients with stage I-III BC. The randomized 2-arm design is adopted to estimate differences in preliminary efficacy estimates between the GET and CBT arms and the GET-only arm. Sample size is estimated based on the A’Hern single-arm decision framework. Under this framework, the combined GET and CBT will be considered feasible and acceptable if at least 70% of patients in the primary study cohort score at least 24 points on the CSQ-8 survey at 3 months and attend at least 3 out of 4 sessions for GET and CBT each. No formal hypothesis testing of between-arm differences will be undertaken, as the study is not powered for comparative efficacy analyses and will focus on generating preliminary estimates of effect.

The study team considers the combination of GET and CBT worthy of further investigation if at least 70% of eligible participants randomized to the GET plus CBT arm find the therapy acceptable and adhere to their therapy sessions. Conversely, the combination therapy will not be worthy of further investigation if the acceptability and feasibility rate is less than 50%. Based on the A’Hern design, the combination of GET and CBT will be worthy of further investigation with 80% power and a 5% significance level if at least 24 of 37 participants find the therapy acceptable and adhere to their therapy sessions. With a 1:1 allocation ratio in this randomized study, a total of 90 participants will be recruited, with 45 participants in each arm, after accounting for dropout. An exploratory study cohort of 10 patients with stage IV BC is included in this study, and the total sample size is 100 participants.

All analyses, except for safety data, will be based on an intention-to-treat approach. Safety data will be reported based on the actual intervention received by participants. Descriptive statistics will be used to summarize participants’ characteristics, the willingness-to-pay survey, safety data, and close-ended participant feedback items. Responses to open-ended questions will be analyzed using descriptive content analysis to identify common themes and illustrative examples. The primary feasibility endpoint will be estimated based on the exact method. The primary acceptability endpoint will be estimated based on a mixed effects logistic regression model. This model will include indicator variables for postbaseline assessment time points and study sites as fixed effects and patient-specific random intercepts. Continuous secondary outcome measures, including FACIT-F, Medication Adherence Scale, FACT-G, GLTPAQ, 6MWT, HGS, and 5-times sit-to-stand test, will be analyzed using mixed effects linear regression models for repeated measures. For each measure, the change in score between assessment time points within each arm and the difference in scores between the 2 arms at the various assessment time points will be estimated and reported with 95% CIs. Each mixed effects linear model will include study arm, indicator variables for postbaseline assessment time points, interaction terms between the time variables and study arm, and study sites as fixed effects and patient-specific random intercepts. Models estimating the difference in scores between the 2 arms at various assessment time points will be further adjusted for baseline score. The choice of the structure used to fit the covariance matrix of each mixed effects model will be assessed at the time of analysis. No imputation for missing data will be carried out, and all patients with nonmissing data at any one of the assessment time points will be included in the analysis. No adjustment for multiple comparisons of secondary outcome measures will be made.

Two sets of analyses will be conducted. The first set will be based on the primary study cohort, and the second set will be based on the combined primary and exploratory study cohorts. For the second set, no hypothesis testing will be conducted. The focus of this set is to generate outcome estimates in all patients with BC to facilitate future study planning.

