### Specific Aims

The coprimary aims are to evaluate: (1) acceptability of GET and CBT, using the Client Satisfaction Questionnaire-8 (CSQ-8), including items on cultural sensitivity; and (2) feasibility of GET and CBT as indicated by participant uptake and adherence to sessions and participants’ willingness to pay for therapy sessions.

We hypothesize that at least 70% of patients with BC will find the combination of GET and CBT to be acceptable and will adhere to their therapy sessions.

The secondary aims include the following:

Assessment of preliminary efficacy in reducing fatigue using the Functional Assessment of Chronic Illness Therapy–Fatigue (FACIT-F) subscaleEvaluation of adherence to BC treatments using self-reported adherence data and estimations from dispensed medication possession ratiosEvaluation of QoL using the Functional Assessment of Cancer Therapy–General (FACT-G) questionnaireAssessment of physical activity and functional outcomes using the Godin-Shephard Leisure-Time Physical Activity Questionnaire (GLTPAQ), 6-minute walk test (6MWT), handgrip strength (HGS), and 5-times sit-to-stand test

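### The coprimary go/no-go decision has two inconsistent pass marks: an observed rate of at least 70%, and the A'Hern count of at least 24 of 37 (64.9%)

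*Protocol article*

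**What the plan says.** All the relevant text is in Statistical Methods of the protocol article.

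- The first paragraph adopts the A'Hern single-arm framework for the combination arm in the stage I-III cohort. It then says that, under this framework, "the combined GET and CBT will be considered feasible and acceptable if at least 70% of patients in the primary study cohort" reach 24 points on the CSQ-8 at 3 months and attend at least three of four sessions of each therapy.
- The second paragraph says the combination is "worthy of further investigation if at least 70% of eligible participants randomized to the GET plus CBT arm" find it acceptable and adhere, and that it "will not be worthy of further investigation if the acceptability and feasibility rate is less than 50" percent.
- The same paragraph then gives the A'Hern result: "with 80% power and a 5% significance level", the combination passes "if at least 24 of 37 participants find the therapy acceptable and adhere to their therapy sessions".
- On numbers, "a total of 90 participants will be recruited, with 45 participants in each arm, after accounting for dropout". No dropout rate is given. The next part of the section adds: "All analyses, except for safety data, will be based on an intention-to-treat approach".

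**The concern.** In an A'Hern design the two rates and the cut-off do different jobs. The null rate (here 50%) and the alternative (here 70%) are assumed true rates. The decision is made on an observed count, which lies between them. The second paragraph follows this logic and arrives at 24 of 37. The first paragraph places 70% on the observed data: it counts patients who reach a score and attend sessions, and says how the result will be judged. Read literally, it is a second and stricter pass mark.

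The rule settles both coprimary aims and is the only formal decision criterion, since between-arm testing is excluded. The trial is also nonblinded. If the 70% sentence is followed, a programme that truly reaches the target fails almost half the time. If neither mark is named as governing, the choice can be made after the results are known. The risk grows if the number analysed is not 37: the article gives no count for any other number, so the 70% figure is the natural one to fall back on.

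**Working it through.** **Inputs**, all from Statistical Methods: null rate p0 = 0.50; alternative p1 = 0.70; significance level 5% (sidedness not stated; the design reproduces as one-sided); power 80%; cut-off 24 of 37; 45 recruited to the combination arm in the primary cohort. The allowance from 45 to 37 is 1 − 37/45 = 17.8%. Under intention to treat the number analysed could be as large as 45, so n from 37 to 45 is examined.

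**Formula.** With X successes among n, X ~ Binomial(n, p). For a rule that passes at X ≥ r, alpha = P(X ≥ r | n, 0.50) and power = P(X ≥ r | n, 0.70). The combined criterion is treated as one yes/no endpoint, as the plan's own calculation appears to do.

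**Step 1: reproduce the plan's figure.** For n = 37 and r = 24, alpha = 0.0494 and power = 0.8071. A search from n = 20 upward finds 37 to be the smallest n with alpha ≤ 0.05 and power ≥ 0.80. The stated design is correct. Its cut-off as a rate is 24/37 = 64.9%.

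**Step 2: use 70% as the observed pass mark.** The count needed is 0.70 × n, rounded up. For n = 37, 25.9 becomes 26; for n = 45, 31.5 becomes 32. The A'Hern columns give the smallest count with alpha ≤ 0.05.

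| n | 70% rule: count | alpha | power | A'Hern count | alpha | power |
|---|---|---|---|---|---|---|
| 37 | 26 | 0.0100 | 0.566 | 24 | 0.0494 | 0.807 |
| 38 | 27 | 0.0069 | 0.524 | 25 | 0.0365 | 0.774 |
| 39 | 28 | 0.0047 | 0.482 | 26 | 0.0266 | 0.740 |
| 40 | 28 | 0.0083 | 0.577 | 26 | 0.0403 | 0.807 |
| 41 | 29 | 0.0058 | 0.536 | 27 | 0.0298 | 0.776 |
| 42 | 30 | 0.0040 | 0.496 | 27 | 0.0442 | 0.836 |
| 43 | 31 | 0.0027 | 0.456 | 28 | 0.0330 | 0.808 |
| 44 | 31 | 0.0048 | 0.548 | 28 | 0.0481 | 0.861 |
| 45 | 32 | 0.0033 | 0.509 | 29 | 0.0362 | 0.836 |

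Power of the 70% rule runs from 0.456 (n = 43) to 0.577 (n = 40). Its alpha never exceeds 0.010.

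**Step 3: where the rules conflict.** At n = 37 the count rule passes 24 (64.9%) and 25 (67.6%), and the 70% rule fails both. At a true rate of 70%, the probability of 24 or 25 is 0.807 − 0.566 = 0.241.

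**Step 4: chance of failing a programme that truly reaches 70%.** Under the 70% rule it is 1 − 0.566 = 0.434 at n = 37 and 1 − 0.509 = 0.491 at n = 45. Under 24 of 37 it is 1 − 0.807 = 0.193.

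**The case against.** The strongest reply is that the section can be read coherently. The second paragraph sets 70% against less than 50%. As observed cut-offs these would leave everything in between undecided, so they make better sense as the alternative and null rates. The A'Hern sentence turns them into the only count given, and that count is the only rule with stated operating characteristics. On this view the 70% sentence in the first paragraph merely names the target. The reply succeeds for the second paragraph but not for the first, which describes how observed scores and attendance will be judged and is introduced as the framework's own rule.

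It is also fair to say that the practical effect is limited. The rules differ at only two counts when n = 37. Significance and Clinical Implications makes progression to a definitive trial depend on a review of all pilot findings, so neither mark alone triggers it. That lowers the stakes, but it does not say which mark decides feasibility and acceptability.

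Three stronger readings are tempting and are not supported:

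- A reader might infer that the stated 80% power is wrong. The article attaches it only to 24 of 37, where it is right.
- A reader might infer from the reference to the primary study cohort that the 70% applies to all 90 patients in both arms. The same paragraph limits the framework to the combination arm, and GET-only patients have no CBT sessions to attend and so could not meet the criterion.
- A reader might take the 70% hypothesis in Specific Aims as a further conflicting rule. It is a statement about the underlying rate, which is the proper use of 70%.

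**Conclusion.** The point stands as an internal inconsistency in a decision threshold. Two pass marks are in print, 70% observed and 64.9% observed, and nothing ranks them. The conflict region has about 24% probability at n = 37 and a true rate of 70%. Following the 70% sentence would cut power from 0.807 to 0.566 at n = 37, and to 0.509 if all 45 are analysed. Type I error is not at risk: the stricter mark only makes a false pass rarer.

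These figures assume a one-sided 5% level, a single combined binary endpoint with a true rate of exactly 70%, and an analysed number between 37 and 45. Because the conflict lies between two printed statements, it cannot be put down to the article being a condensed account.

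**What to change.** Before analysis starts:

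1. Reword the 70% sentence in the first paragraph of Statistical Methods so that 70% is the target, meaning the assumed true rate, and not the observed pass mark.
2. State the null rate as 50%, the alternative as 70%, and the 5% level as one-sided if that is what is meant.
3. Keep one pass mark: the A'Hern count for the number analysed in the stage I-III GET plus CBT arm. This is 24 if 37 are analysed and 29 if 45 are (alpha 0.036, power 0.836). For numbers in between, fix the counts in advance from the table above, noting that power falls slightly short of 80% at 38, 39 and 41.

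The cost is a wording change in the protocol and analysis plan, with no new data and no more patients. The Results section says analysis had not begun at submission, so the rule can still be settled before outcomes are known.

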### Measures

#### Primary Endpoints

The primary acceptability endpoint is defined as the percentage of participants who score at least 24 (out of a maximum of 32) on the CSQ-8 survey at 3 months. The primary feasibility endpoint is defined as the percentage of participants who are adherent to their therapy sessions (attending at least 3 out of 4 sessions for GET and CBT each).

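### The coprimary acceptability percentage is to be estimated from a random-intercept logistic model that matches neither its definition as a 3-month percentage nor the 24-of-37 decision count

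*Protocol article*

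**What the plan says.** The Primary Endpoints section of the protocol article defines acceptability as the "percentage of participants who score at least 24 (out of a maximum of 32) on the CSQ-8 survey at 3 months". This is one proportion at one time point.

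Statistical Methods sizes and decides the coprimary aims with A'Hern's single-arm design. The combination merits further study "if at least 70% of eligible participants randomized to the GET plus CBT arm find the therapy acceptable" and adhere to their sessions. It does not if the rate is below 50%. The operating rule is stated "with 80% power and a 5% significance level if at least 24 of 37 participants find the therapy acceptable" and adhere. The same section also words the rule as a percentage: the combination "will be considered feasible and acceptable if at least 70% of patients in the primary study cohort score at least 24 points" and meet the attendance requirement.

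Later in Statistical Methods the two coprimary endpoints receive different estimators. Feasibility is estimated by the exact method. For acceptability: "The primary acceptability endpoint will be estimated based on a mixed effects logistic regression model". On its terms: "This model will include indicator variables for postbaseline assessment time points and study sites as fixed effects and patient-specific random intercepts". The section does not say whether the reported figure is averaged over the random intercept and sites, or how it relates to the 24-of-37 count or the 70% wording.

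**The concern.** The endpoint is a population percentage and the decision rule is a binomial count. The named estimator is neither. In a random-intercept logistic model the fixed effects describe a patient whose random effect is zero, at a particular site. Because the logistic curve is not linear, the probability for that patient differs from the average probability over all patients. Above 50% it is the larger of the two, and the gap grows with the between-patient SD.

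Two things are at stake. First, the reported acceptability figure could exceed the percentage that the Primary Endpoints section defines. Second, the stated 5% significance level and 80% power are properties of counting successes among 37 participants. They do not describe a model estimate set against the same threshold. Acceptability is one of two coprimary endpoints and feeds the decision on a definitive trial.

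**Working it through.** **Inputs from the protocol article (Statistical Methods).** Unacceptable rate 50%, desired rate 70%, 5% significance, 80% power, rule 24 of 37, 45 recruited per arm. One-sided exact testing is assumed, as is usual for A'Hern; the article does not state the sidedness.

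**Input assumed.** Random-intercept SD on the logit scale, σ. The document gives no value. I show 0.5, 1 and 2, with 3 as an extreme (latent intraclass correlation σ²/(σ² + π²/3) = 0.07, 0.23, 0.55 and 0.73).

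**Step 1: reproduce the plan's rule.** With X ~ Binomial(37, p):
- P(X ≥ 24 | p = 0.50) = 0.0494
- P(X ≥ 24 | p = 0.70) = 0.807
- A cut-off of 23 would give alpha 0.0939, so 24 is the correct cut-off. 37 is the smallest n meeting both limits.

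The stated design is correct for a count.

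**Step 2: convert a true percentage to the patient-specific probability.** For a true percentage m, solve m = E[expit(a + σZ)], Z ~ N(0,1), for a by Gauss-Hermite quadrature, then read off expit(a). Example: m = 0.70 and σ = 2 give a = 1.384 and expit(1.384) = 0.800.

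| True percentage | σ = 0.5 | σ = 1 | σ = 2 | σ = 3 |
|---|---|---|---|---|
| 50% | 50.0% | 50.0% | 50.0% | 50.0% |
| 60% | 60.6% | 62.0% | 66.1% | 70.7% |
| 65% | 65.8% | 67.8% | 73.4% | 79.2% |
| 70% | 71.0% | 73.5% | 80.0% | 86.1% |

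In reverse, a patient-specific 70% corresponds to a true 69.0%, 66.9%, 62.6% or 59.6%.

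**Step 3: effect on a threshold, if the patient-specific figure were used.** Simulation with 37 patients, three post-baseline visits, no site effects, maximum likelihood, 300 runs per setting (simulation error about 1 to 3 percentage points). Each row compares like with like.

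| Cut-off and true rate | Observed proportion or count | Patient-specific, σ = 1 / 2 / 3 |
|---|---|---|
| 24/37 (64.9%), true 50% | 4-5% (exact 4.9%) | 6% / 15% / 24% |
| 24/37 (64.9%), true 60% | 31-35% (exact 33%) | 41% / 61% / 65% |
| 70%, true 60% | 12-14% (exact 13.3%) | 21% / 39% / 53% |

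At a true 50% the patient-specific value is not shifted; more false passes occur because the estimate is more spread out.

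**Step 4: the same model, averaged over the random intercept.** At a true 60%, the marginalised estimate reached 70% in 9-14% of runs, against 12-14% for the observed proportion. The problem therefore lies in which quantity is taken from the model.

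**Step 5: the cut-off depends on the denominator.** For n = 45, P(X ≥ 28 | 0.50) = 0.0676 is too large. P(X ≥ 29 | 0.50) = 0.0362, with P(X ≥ 29 | 0.70) = 0.836. The 70% wording is a different rule again: with 37 patients it needs 26 (0.70 × 37 = 25.9), which has alpha 1.0% and power 56.6%.

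**The case against.** The strongest defence is that the article names a model without saying that the patient-specific probability will be reported. The endpoint is defined as a percentage of participants, which the same model yields once averaged, and that step could sit in an analysis plan not shown here. The decision rule is already worded as a count, and the estimation paragraph does not replace it. Success also requires adherence, estimated exactly, and the section on significance and clinical implications bases progression on a review of all pilot findings. All of this stands and limits the point: overstatement is conditional. It does not remove the point, because the text assigns a specific estimator to a coprimary endpoint, that estimator does not match the rule, and nothing connects the two.

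A reader might infer three stronger claims that the document does not support.

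- **That the model mixes in GET-only patients because it has no study-arm term.** Statistical Methods applies the single-arm framework to the combination arm and refers to participants randomised to it. A model fitted in one arm needs no arm term. The primary study cohort there separates stage I-III from the set that adds stage IV; it does not define the arm.
- **That the estimate is biased upward against the 50% standard.** At a true 50% there is no shift.
- **That any pass rate above that of an observed 70% measures the harm.** The 24-of-37 rule itself passes 58% of the time at a true 65% and 33% at a true 60%. Comparing the model with an observed-70% criterion alone therefore exaggerates its effect relative to the A'Hern rule.

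The model does have one advantage: it uses 6- and 12-month responses and accommodates missing 3-month scores without imputation.

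**Conclusion.** The concern holds in a conditional form. The stated estimator for acceptability fits neither the endpoint's definition nor its decision rule, and the A'Hern error rates do not apply to its output. If the patient-specific probability is reported or set against 70% or 24/37, a true 70% is overstated by 1.0, 3.5 or 10.0 percentage points, and a true 65% by 0.8, 2.8 or 8.4 points, at an assumed SD of 0.5, 1 or 2. The size rests entirely on that SD: it is minor at the low end and could change the decision at the high end. If the model output is averaged over intercepts and sites, the shift disappears, although the exact error rates still belong to the count. The document does not show that a false pass will occur. It leaves the route to one open for a coprimary endpoint.

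**What to change.** 1. Make the primary acceptability estimate and decision the observed number of stage I-III patients randomised to GET plus CBT with a CSQ-8 score of at least 24 at 3 months, with an exact confidence interval, as for feasibility.
2. Take the A'Hern cut-off for the actual denominator: the smallest r with P(X ≥ r | n, 0.50) ≤ 0.05. This is 24 for n = 37 and 29 for n = 45 (exact alpha 3.6%, power 83.6% at 70%). A denominator of all 45 randomised should not be paired with the cut-off built for 37. State this as the single rule in place of the separate 70% wording.
3. State in advance how missing 3-month scores count.
4. Keep the mixed logistic model as supportive, fitted in that arm and reported as population-averaged 3-month percentages.

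**Cost.** This is a change of wording only; sample size and data collection are unaffected, and the Results section says that analysis had not begun. The 6- and 12-month responses no longer inform the primary estimate. If missing scores count as failures, power falls: with 8 of 45 missing, a true 70% becomes 0.70 × 37/45 = 57.6%, and P(X ≥ 29 | 45, 0.576) is about 22%. The missing-score rule should therefore be chosen with that loss in view.

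### Participants who never return a CSQ-8 are left out of the coprimary acceptability estimate, which may then be too high; an all-randomized bound with its own cut-off should stand beside it

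*Protocol article*

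**What the plan says.** All of this is in the Methods of the protocol article.

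- **Endpoint** (Primary Endpoints): acceptability is "the percentage of participants who score at least 24 (out of a maximum of 32) on the CSQ-8 survey at 3 months".
- **Decision criterion** (Statistical Methods): the combination merits further study if "at least 70% of eligible participants randomized to the GET plus CBT arm find the therapy acceptable"; session attendance has to reach the same mark. It does not merit further study "if the acceptability and feasibility rate is less than 50" percent. The operating rule is 24 of 37 at a 5% level with 80% power, and each arm is enlarged to 45 for dropout.
- **Analysis population** (Statistical Methods): "All analyses, except for safety data, will be based on an intention-to-treat approach".
- **Estimator** (Statistical Methods): acceptability comes from a logistic model with mixed effects. Its terms are given as follows: "This model will include indicator variables for postbaseline assessment time points and study sites as fixed effects and patient-specific random intercepts".
- **Missing data** (Statistical Methods): "No imputation for missing data will be carried out, and all patients with nonmissing data at any one of the assessment time points" enter the analysis.

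The article does not say how a randomized participant with no CSQ-8 counts towards the acceptability criterion.

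**The concern.** A satisfaction score has no pre-treatment value, and the first scheduled outcome visit after baseline is at 3 months. A participant who withdraws completely before then, which the Expected Risks section allows, has no CSQ-8 at all. Under the stated rule that person is in neither the numerator nor the denominator of the acceptability estimate.

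A mixed model can make up for a missing visit by borrowing from the same person's other visits. For someone with no visits there is nothing to borrow, and the model has no attendance, withdrawal or baseline covariate that could stand in. Such people are in effect taken to be like the responders.

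For most outcomes that may be tolerable. For acceptability, leaving can itself be a sign that the programme was not acceptable. One of the two coprimary results could then describe satisfaction among those who stayed, although the criterion is worded on those randomized.

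**Working it through.** **Inputs from Statistical Methods:** unacceptable rate 50%, target rate 70%, 5% level, 80% power, rule 24 of 37, 45 per arm. The dropout rate is not given. The step from 45 to 37 implies 8 losses, 8/45 = 17.8%.

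**Step 1: reproduce the plan's rule** (exact binomial, one-sided).
- P(X ≥ 24 | n = 37, p = 0.50) = 0.049
- P(X ≥ 24 | n = 37, p = 0.70) = 0.807

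The rule holds as stated, provided the 37 represent the population of interest.

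**Step 2: effect on the estimate.** Take 26 of 37, the smallest count that reaches 70% (0.70 × 37 = 25.9). Let q be the share of the 8 non-returners who were in truth satisfied; q is an assumption. The rate over all randomized is (26 + 8q)/45.

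| q | Rate over all 45 | Excess of 70.3% over it |
|---|---|---|
| 0 | 26/45 = 57.8% (exact 95% CI 42.2% to 72.3%) | 12.5 points |
| 0.20 | 27.6/45 = 61.3% | 9.0 points |
| 0.50 | 30/45 = 66.7% | 3.6 points |
| 0.703 | 70.3% | 0 |

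**Step 3: effect on the acceptability decision.** Suppose the true rate over all 45 is 50%, so the programme should fail. The rate among the 37 returners is (0.50 × 45 − 8q)/37.
- q = 0: 22.5/37 = 60.8%, and P(X ≥ 24 of 37) = 0.37
- q = 0.25: 20.5/37 = 55.4%, and P(X ≥ 24 of 37) = 0.16
- q = 0.50: 18.5/37 = 50.0%, and P(X ≥ 24 of 37) = 0.049, the planned value

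**Step 4: does the planned model correct this?** Steps 2 and 3 use raw proportions, so the mixed model was also simulated: 45 participants, three visits, random-intercept SD 2 (assumed), true 3-month rate about 50%, and missingness falling on roughly the 8 least satisfied.
- All 8 missing at every visit: mixed model 58.2%, complete case 58.2%.
- 4 of the 8 return at later visits: mixed model 56.5%, complete case 58.7%.

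The model helps a little when non-returners come back later, and not at all when they never do.

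**Step 5: cut-off for the full denominator.** The rule of 24 was derived for 37 and does not carry over to 45. With n = 45, at least 29 gives one-sided alpha 0.036 and power 0.836 at a true 70% if every form is returned. A cut-off of 28 would give alpha 0.068, above 5%.

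**Step 6: cost of counting missing as not acceptable.** Suppose the true rate is 70% and forms are missing for unrelated reasons.
- 8 missing: 29 of 37 returners must score at least 24; probability 0.18.
- 4 missing: 29 of 41 must; probability 0.54.

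At q = 0.20 to 0.50, the 57.8% from this rule is also 3.6 to 8.9 points too low, nearly a mirror image of the responder figure's excess.

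**The case against.** The other side has several sound points.

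- **The direction is not established.** The documents give no dropout rate and nothing that ties loss to dislike. Strengths and Limitations foresees technology barriers, which could produce missing forms unrelated to satisfaction. If non-returners were as satisfied as returners, there is no bias. This stands: the estimate may be biased, not is.
- **Stopping sessions is not the same as leaving the study.** Surveys are electronic and outcomes are assessed at 3, 6 and 12 months. A person who stops therapy can still return a form, and one with only a later CSQ-8 stays in the model. This stands: the gap concerns those who return none.
- **Attendance is a coprimary requirement.** The programme must also show adherence, defined as at least 3 of 4 sessions of GET and of CBT. Early quitters can be counted there as non-adherent without a survey. A reader might infer that the go decision can rest on attrition alone; the documents do not support that. The protection is partial, since 8 quitters still leave 37 of 45 who could be adherent, and it does nothing for the acceptability estimate.
- **Intention-to-treat wording.** Analysing by allocated arm with all observed data is a common reading of the term, so the label alone is not an error. The mismatch that remains is between a criterion worded on those randomized and an estimate based on responders.
- **Sensitivity analyses may sit in an unseen analysis plan.** True, and their absence from the article is not the point. The article does fix a no-imputation rule and the model terms, and those have the effect described.
- **Missing as failure is biased too.** Step 6 shows this. It rules out that approach as the sole primary analysis, but not as a stated bound.

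**Conclusion.** The concern holds in a limited form. Under the stated rule and model, participants randomized to GET plus CBT who return no CSQ-8 do not count in the coprimary acceptability estimate, although the criterion is worded on those randomized and the sample size expects loss.

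If non-return is linked to dissatisfaction, the estimate may be too high. At the plan's own implied loss of 8 in 45, the excess is about 4 to 9 points if 20% to 50% of the missing were satisfied, and 12.5 points if none were. In that last case, a programme with a true rate of 50% would meet 24 of 37 with probability 0.37 instead of 0.049. All these figures rest on assumed satisfaction among non-returners and on 8 losses; they are zero or small if forms are missing for unrelated reasons or few are missing.

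A reader might infer that the result is certain to be inflated, or that missing-as-failure is the correct primary analysis. The documents support neither. The point deserves a change because an acceptability conclusion could otherwise rest on responders without showing it, and the pilot's findings are meant to decide whether a definitive trial goes ahead.

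**What to change.** 1. Prespecify a second acceptability analysis in all stage I-III participants randomized to GET plus CBT, with a missing 3-month CSQ-8 counted as not acceptable and an exact confidence interval.
2. Give it its own cut-off: at least 29 of 45 (one-sided alpha 0.036; power 0.836 if all forms are returned). If the number randomized differs from 45, recompute the cut-off in the same way.
3. Report it beside the planned mixed-model estimate, with the number who returned no CSQ-8. Describe acceptability as robust only if both support it.
4. Keep the planned model. The new analysis bounds it and does not replace it.

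**Cost:** wording only, with no new data. The Results section says data analysis had not begun at submission, so this can still be prespecified. The downside should be stated in the plan: the bound is conservative, and at a true 70% it is met with probability only about 0.18 if 8 forms are missing for unrelated reasons (0.54 if 4 are). Failing the bound alone should therefore be read as uncertainty due to missing forms, not as evidence that the programme is unacceptable.
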